## Abstract

**Background:**

The pre-school years are considered critical for establishing healthy lifestyle behaviours such as physical activity. Levels of physical activity track through childhood into adulthood, thus establishing habitual physical activity early in life is vital. Time spent outdoors is associated with greater physical activity and playground interventions have been shown to increase physical activity in school aged children. There are few pre-school, playground-based interventions, and evaluations of these have found mixed results. A recent report published by the UK Chief Medical Officer (CMO) highlighted that new interventions to promote movement in the early years (0–5 years old) are needed. The aim of this study is to undertake a pilot cluster randomised controlled trial (RCT) of an outdoor playground-based physical activity intervention for parents and their children aged 18 months to 4 years old (“Pre-schoolers in the Playground”; PiP) and to assess the feasibility of conducting a full scale cluster RCT. The PiP intervention is grounded in behavioural theory (Social Cognitive Theory), and is in accordance with the CMO guidance for physical activity in the early years. It is informed by existing literature and data collected from focus groups with parents.

**Methods/Design:**

One hundred and fifty pre-school children affiliated to 10 primary schools will be recruited. Schools will be randomised to either the PiP intervention arm or the control arm (usual practice). Children in the intervention arm will be invited to attend three 30 minute outdoor play sessions per week for 30 weeks (3 school terms) at the school. Feasibility will be assessed by examining recruitment rates, attendance, attrition, acceptability of the trial and of the PiP intervention to parents, fidelity of intervention implementation, capability and capacity for schools to deliver the intervention. Health outcomes and the feasibility of outcome measurement tools will be assessed. These include physical activity via triaxial, accelerometry (Actigraph GT3X+), anthropometry (height, body mass, BMI, waist and upper arm circumference), health related quality of life for child (PedsQL) and parent (EQ5D), parent wellbeing (ComQol-A5), injuries and health service use. A health economic evaluation will also be undertaken.

**Discussion:**

It is anticipated that results of this pilot trial will be published in spring 2015.

**Trial registration:**

Current controlled trials: ISRCTN54165860

## Background

### Physical activity and the pre-school years

The pre-school years are considered a critical period for establishing healthy lifestyle behaviours such as physical activity [1]. The benefits of engaging in regular physical activity in the pre-school years are numerous, with one of the most significant being the promotion of healthy weight and prevention of obesity during childhood [2-5]. In pre-school children the prevalence of overweight and obesity has doubled in recent decades [6] and in the mid-2000s over a third of pre-school children in the UK and US were overweight and obese [7]. Despite the widespread belief that the prevalence of childhood obesity is still escalating, contemporary high-quality studies suggest a slowing in the rate of rise in some developed countries including the UK [8,9]. Whilst this appears promising, levels still remain high and are heterogeneous within countries [8]. For example, in England childhood obesity is higher in urban areas, in children from deprived backgrounds and in certain ethnic minority groups, including Black and Asian populations [10]. Also, South Asian school-aged children are reported to have substantially lower levels of physical activity than White Europeans [11]. These particularly low levels may contribute to the increased risk of obesity, coronary heart disease and diabetes seen in South Asians living in the UK [12].

Observational and experimental studies have shown that regular physical activity has other important health and social implications for pre-school children. Physical activity is valuable for developing motor skills, enhancing bone and muscle development and for social competence [13,14]. Furthermore, regular physical activity in this age group may also have beneficial effects upon cardiovascular disease risk factors including more favourable blood pressure and blood lipids [14-16]. Finally, levels of physical activity track through early childhood [17] and into adulthood, [18,19] thus, establishing habitual physical activity early in life may be key to remaining active throughout the lifespan.

Current levels of habitual physical activity in pre-school children in the UK and internationally are unclear. Methodological differences in the objective measurement of physical activity have resulted in a wide variation of levels reported. Daily physical activity levels have been reported to be as low as 90 minutes in the UK [20], with higher levels of 127 minutes per day reported in Belgium, Australia and the USA, [21-23] and 402 minutes in Portugal and the USA [22,24]. This large variation in reported physical activity behaviour is likely due to the application of different intensity cutpoints to accelerometry data (that is, cutpoint non-equivalence [25]) between different research groups, rather than actual behavioural differences between countries. Despite the lack of clarity regarding the extent of physical activity that pre-schoolers engage in, it has been clearly identified that health-enhancing physical activity declines markedly during childhood [26], with this decline potentially beginning in the early years [27]. Therefore the promotion of physical activity in the pre-school years is critical for the prevention of this age-related decline.

### UK physical activity policy for pre-school children

The importance of engaging pre-school children in daily physical activity was brought to the forefront in July 2011 with the publication of the UK’s first physical activity guidelines for children under 5-years-old in the Chief Medical Officer’s (CMO) report *start active, stay active*[28]. The report recommends 180 minutes of physical activity (light, moderate and vigorous intensity) each day, and states that the volume of physical activity is more important than the intensity. Physical activity should be spread throughout the day and include active play (activities that involve movements of all the major muscle groups), and the development of locomotor, stability and object-control skills.

These guidelines are a significant step in recognising the importance of physical activity promotion for pre-school children; however, guidelines themselves do not change behaviour. The determinants of physical activity in young children are unclear; one systematic review that studied correlates of pre-schoolers’ physical activity found that boys were more active than girls and that parents’ levels of physical activity and a child’s time spent outdoors had a positive association with physical activity [29]. Additionally, preliminary findings from an ongoing systematic review suggest that providing easy-access environments that facilitate physical activity are important [30]. The CMO report states that a ‘concerted and committed action to create environments and conditions that make it easier for people to be more active is needed [28, page 8]. The guidelines highlight the need for activities to promote movement in the early years and recognise that local communities can have a strong influence on behaviour. The report suggests investment in community level programmes in settings such as school playgrounds. We therefore aim to develop and evaluate such an intervention in an area of ethnic diversity and social deprivation in West Yorkshire, UK.

### Components of successful interventions

There are several features of successful interventions identified in the literature, which have informed the intervention reported here.

#### A) Theoretical underpinning

The utility of basing health promotion interventions upon sound theoretical frameworks is well-expounded [31]. A systematic review [32] conducted by members of our team ([name], [name]) reported that the predominant behavioural change theory used in successful childhood obesity prevention interventions is Bandura’s social cognitive theory (SCT) [33,34]. This theory describes behavioural change as an interaction between personal*,* environmental and behavioural factors. Personal and environmental factors provide the framework for understanding behaviour. Some of the personal concepts include skills, self-efficacy, self-control and outcome expectancies, whereas environmental concepts include availability (for example, provision of space for physical activity) and opportunity for social support (for example, a group setting). The review also reported that providing information on behaviour-health links appeared to be an important component in childhood obesity prevention/physical activity interventions.

#### B) An outdoor setting

Enhancing environmental and cultural practices that support children to be more active throughout the day are thought to be promising strategies to prevent childhood obesity, particularly if the children perceive them as being fun [35]. Time spent outdoors correlates with physical activity levels in pre-school children [29] and outdoor play is associated with a lower risk of being overweight [36]. Indeed, in school-aged children, outdoor playground interventions have increased physical activity [37,38]. Furthermore, factors associated with increased moderate to vigorous physical activity (MVPA) in playground interventions are greater provision of equipment [37,38] and greater play space per child [39]. Interventions in pre-school playgrounds supervised by pre-school teachers, however, have had mixed success. Adding portable play equipment in a US pre-school playground increased physical activity levels in 3- to 5-year-olds [40]. In contrast, in Belgium, no change in physical activity levels of 4- and 5-year-olds was reported after providing playground markings, or play equipment or both in the pre-school playground [41]. The authors concluded that creating an activity-friendly environment may not be sufficient to promote physical activity in pre-schoolers and regular infusions of different equipment with more guidance and encouragement from adults to play in an active way is required. Currently there is no evidence regarding pre-school playground interventions from the UK.

#### C) Parental involvement

Parental engagement should be a key part of any intervention in the pre-school years [42] and the suggestion that adult encouragement is required to increase active play is supported by findings from a systematic review of pre-school obesity prevention interventions [43]. Twelve interventions reported in another obesity prevention systematic review were conducted in a variety of settings (pre-school/childcare, home, group, primary care and mixed settings) and included a physical activity component. Home-based interventions appeared to be the most successful at increasing physical activity despite the small sample sizes of studies and poor adherence to the interventions. This is perhaps due to parental involvement in the interventions, which has been suggested to be vital for facilitating behavioural change during the early years [32]. Mothers in particular are considered to play a major role in establishing a child’s health lifestyle behaviour [44], and this in part may be indirectly through modelling of behaviours [45].

### Aim

The aim of this paper is to describe the protocol, Pre-schoolers in the Playground (PiP), for a pilot cluster randomised controlled trial (RCT) of an outdoor playground-based physical activity intervention for parents and their children aged 18 months to 4 years, which will assess the feasibility of conducting a full-scale cluster RCT.

## Design and methods

### Study design

The design of this pilot study is based on guidance from the UK Medical Research Council for developing and evaluating complex interventions [46]. Figure 1 shows the trial design; the trial is a two-armed pilot cluster randomised controlled trial with economic and qualitative evaluations. The two arms are PiP intervention and usual practice (control). Recruitment, randomisation and the intervention or control period will take place in three waves. Wave 1 commenced in the autumn 2012 school term, Wave 2 commenced in the spring 2013 school term and Wave 3 will commence in the summer 2013 school term. This staggered approach will allow the examination of seasonal variations in the feasibility of the study and the intervention. The intervention comprises a 10-week initiation phase (one school term) followed by a 20-week maintenance phase (two school terms). Follow up will be at 10 weeks, (mid-intervention), 30 weeks (at the end of the intervention) and 52 weeks. This study has been ethically approved by the NRES Committee Yorkshire and The Humber - Bradford (reference: 12/YH/0334) and complies with the Declaration of Helsinki.

**Figure 1 F1:**
[figure not shown]
**“Pre-schoolers in the playground” (PIP) pilot trial flow-diagram.** BMI, body mass index.

### Setting

The setting for the trial is Bradford, West Yorkshire, UK. Bradford is the sixth largest metropolitan borough in England with a population of approximately 500,000 and includes some of the most deprived areas in the UK [47]. The national child measurement programme for 2010 to 2011 reports that 22% of children in reception and 35% of children in Year 6 in Bradford are overweight or obese [10]. Additionally, the city has very low levels of participation in school sport [48]. Half of all of babies born in Bradford are of South Asian origin (mainly of Pakistani and Bangladeshi heritage) [49] and 60% of these are born into the poorest 20% of the population of England and Wales based on the index of multiple deprivation (IMD) [47].

### School recruitment

Ten primary schools will be recruited from the 122 primary schools in Bradford, between September 2012 and April 2013. Two primary schools will have associated Children's Centres located on the school site. This is so that the feasibility of conducting the study either at a primary school only, or a joint primary school and children’s centre can be assessed.

Primary schools have been chosen as the site for intervention delivery because of their strong links with other early years services and in order to engage with children from hard-to-reach families who have an older sibling attending the school and do not attend any other early years services. In England early years services include nursery classes held on a primary school site, private day nurseries, pre-schools, independent schools, child minders and Children’s Centres. Children’s Centres are often government funded (Sure Start Children’s Centres). They provide support for young children and families and are particularly focused on the most disadvantaged families, in order to reduce inequalities in child development and school readiness. Children’s Centres work closely with other early years services (nurseries and schools); they can be located on the same site as other services (that is, on the same site as a primary school), or at a separate site.

The study was initially publicised to primary schools though advertising and presentations at education conferences and events hosted for Bradford primary school staff. Recruitment will be through telephone contact and visits to schools. Each study site will complete a study site agreement, which will be signed by the Head teacher and Chair of Governors. Schools that are located in the two poorest quintiles of IMD for Bradford, and that are located across the city of Bradford (Bradford South, West, East and Shipley) will be selected. We estimate, using the *English Indices of Deprivation* 2010 for Bradford District [47], that >80% of schools in Bradford will fall into the two poorest quintiles of IMD. To express thanks for participating in the pilot trial, all schools will receive a donation of £200 towards play equipment. Because the children are pre-school age and not attending the primary school, those affiliated to the schools in the control arm will not have access to the play equipment during the trial period.

### Participant recruitment

Families from participating schools and families who use children’s services that are affiliated with the school (for example, Children’s Centres or nurseries feeding those schools) will be approached to take part in the trial. Recruitment will be via letters home with school-going children and through face-to-face conversations with research assistants in school playgrounds and Children’s Centres or nurseries. To account for the linguistic diversity among the study population, research staff recruiting families and conducting measurements and questionnaires will be bilingual and will undertake these tasks in either English or Urdu [49]. Urdu is the language spoken and understood by Pakistanis. It is also spoken and understood in many parts of Bangladesh. For Bangladeshi participants who do not fully understand Urdu, the consent forms will also be audio-recorded in Syleti and participants will be asked to sign a paper copy of the consent form (translations and transliterations will be prepared in collaboration with staff involved in the cohort study, Born in Bradford, according to standard Born-in-Bradford procedures) [49]. Written informed consent will be gained from all participants at the beginning of the trial. All families will receive a £10 voucher for a children’s shop as a thank you for attending each study measurement session (baseline, 10-, 30- and 52-week follow up) and for participating in a qualitative interview.

### Inclusion criteria

Children will be included if they are aged between 18 months and 4 years and are available to complete three school terms of the intervention before going into Reception class (first year of school).

### Exclusion criteria

Children will be excluded if their parent is unable to provide informed consent.

### Randomisation and blinding

Randomisation will be carried out by York Trials Unit Randomisation Service using a secure computer system. Once baseline data have been collected, participating schools will be randomly allocated to one of the two arms, PiP intervention or usual care (control), on an equal basis (that is, five schools in each arm). Since ethnicity may be an important predictor of physical activity [11] and thus, to avoid chance imbalance in ethnicity, schools will be stratified and blocked by ethnicity (> 50% South Asian pupils or > 50% White pupils).

Blinding of the trial coordinator, schools, participants, and parent-involvement workers/early-years staff will not be possible. The community research assistants who will be assessing outcome measures will be blinded to each school’s allocation as will the statistician and health economists performing the data analyses.

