### Injuries and health service use

Number and type of injuries sustained during the intervention/usual care period and the consequence of the injury (that is, medical attention from General Practitioner, or hospital visit) and service use (health and social care) will be reported by parents and recorded at each assessment point using previously developed questionnaires.

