### Data analysis

#### Statistical analysis

For both arms the numbers of schools and children screened, randomly assigned, receiving PiP or usual care, completing the study protocol, and providing outcome data will be summarised. The number of children withdrawing from the intervention and/or the trial, and where available the reasons for withdrawal, will be summarised by arm. For each data collection point the number of non-attenders will be calculated for each arm and attendance rates compared.

Whilst the main aim of this study is to establish practicality, feasibility, recruitment rates and samples size in order to inform a full-scale trial, and although it is unlikely that the small sample size will result in effectiveness being established, the primary outcome for a full trial, daily MVPA, will be analysed to mimic practice in a full-scale trial. Results from this analysis will be treated as preliminary and interpreted with caution [68,69]. As the number of clusters is low, cluster summary statistics will be utilised rather than multi-level modelling [70,71]. The analysis will be carried out using the school as the unit of analysis and the mean MVPA per day for the individuals in the school as the outcome variable. A weighted linear regression model will be used to compare the intervention and usual-care arms weighted by the number of participants followed up in each cluster and adjusted for the baseline average MVPA per day for each cluster. We acknowledge that participation in a physical activity trial may in effect be an intervention in itself for the control group. Therefore the difference in health outcomes (physical activity and anthropometry) between the intervention and control arms will provide meaningful data on the potential effectiveness of the intervention. We will assess whether playground environment and local environment have a significant impact upon intervention uptake, attendance and changes in levels of physical activity. If they are found to be significant we will consider stratifying schools according to their environment in the full trial.

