#### Health economics analysis

The possibility of using routine databases to capture relevant resource use will be explored and this will be supported by parent and child quality-of-life questionnaires (PedsQL, EQ5D and ComQol-A5), and parent-reported injuries and service use at each assessment time point.

If the data can be collected reliably, an exploratory evaluation will assess whether the addition of the PiP intervention is likely to be cost-effective in the pilot trial. It is acknowledged that the benefits of PiP may be generated over a longer time frame than captured by the trial. We will thus conduct a within-trial analysis and, if possible, an analysis of the costs and benefits associated with the intervention modelled over a more appropriate time horizon. A key part of the economic analysis will be to identify potential sources of data to populate a longer term economic model. In addition, the delivery costs and the resource use associated with the intervention (for example, health service usage including General Practitioner visits, or Accident and Emergency attendances) will be estimated.

Unit costs estimated from the published literature and government sources will be presented. These unit costs will then be applied to the relevant resource use. Each total cost item will then be summed to generate a total cost per trial participant. For this exploratory analysis, where it is considered appropriate, cost and quality-adjusted life year (QALY) data will be synthesised to generate an incremental cost-effectiveness ratio (ICER) where the additional cost of the intervention is formally compared with the additional benefit. Probabilistic sensitivity analyses will be conducted to characterise the uncertainty around the adoption decision (depicted using cost-effectiveness acceptability curves) and to assess the potential and value of further research in this area.

The trial assesses a large number of primary and secondary outcomes. Hence, for a complete picture of the trials results, all the costs and outcomes will be presented in a descriptive and disaggregated way. A review of the literature will be conducted to establish whether it is possible to make links between short-term outcomes measured in the trial and longer-term quality of life, and therefore populate the model.

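### The blinding claimed for the statistician and health economists cannot hold for the economic analysis or for the PiP uptake, attendance and withdrawal analyses

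*Protocol article*

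**What the plan says.** *Randomisation and blinding* in the Protocol article divides the trial's personnel in two. On the open side: "Blinding of the trial coordinator, schools, participants, and parent-involvement workers/early-years staff will not be possible". On the blind side: "The community research assistants who will be assessing outcome measures will be blinded". The blind is to school allocation, and the same sentence extends it to the analysts: "as will the statistician and health economists performing the data analyses". Nothing restricts the second statement to particular analyses or to a period before data are merged.

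Later sections give these analysts their work. *Health economics analysis* calls for estimates of "the delivery costs and the resource use associated with the intervention" and then says: "Each total cost item will then be summed to generate a total cost per trial participant". Where appropriate, costs and QALYs are combined in an ICER, with acceptability curves. *Statistical analysis* asks for summaries by arm of who received PiP and who withdrew from it, and adds: "We will assess whether playground environment and local environment have a significant impact upon intervention uptake, attendance" and changes in physical activity. *Usual practice arm (control)* says that control families have no playground intervention.

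On the assessors, *Participant recruitment* says that "research staff recruiting families and conducting measurements and questionnaires will be bilingual". *Injuries and health service use* has parents report at each assessment point, beginning with: "Number and type of injuries sustained during the intervention/usual care period".

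**The concern.** A blinding statement tells the reader which results were protected from knowledge of the arm. Here it covers analyses that consist of handling data from one arm only. If the pilot's report repeats it, readers will credit the economic and process results with a protection they never had, and the full trial may copy the same sentence.

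The practical stake lies in the order of work. The comparison of MVPA, the intended primary outcome of the full trial, can be done blind. It stays blind only if the analyst has not already opened attendance or cost files. A statement that everything is blinded gives no reason to keep that order.

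**Working it through.** The document states no figure for this point. The check sets the blinding statement beside each assigned task.

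**Inputs.** From *Sample size*: 10 schools, 5 per arm, 15 children per school. These agree with each other: 10 × 15 = 150 and 5 × 15 = 75 per arm.

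**Which data exist in which arm**

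| Task | Section | PiP schools | Control schools |
|---|---|---|---|
| Delivery cost | Health economics analysis | present | none |
| PiP uptake and attendance | Attendance and attrition; Statistical analysis | present | none |
| Withdrawal from the intervention | Statistical analysis | possible | not possible |
| MVPA, anthropometry, questionnaires | Health outcomes | present | present |

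The first three rows differ in kind between the arms. The last does not.

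**What coding protects.** Ten schools can be split 5:5 in C(10,5) = 252 ways, and in fewer once the ethnicity strata are respected. An analyst given schools grouped as A and B faces 2 possibilities. One non-zero attendance count or delivery cost leaves 1. Because allocation is by school, that single item settles all 10 schools and all 150 children.

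**Economic analysis.** Delivery cost enters the total for PiP children only, so the cost file itself shows the arm. The ICER has the form (C_A − C_B) / (E_A − E_B). Swapping A and B changes the sign of numerator and denominator together, so the ratio is unchanged, but its meaning is not. The same positive ratio arises whether PiP costs more and does better or costs less and does worse. An acceptability curve gives the probability that PiP is cost-effective; with labels swapped in a two-arm comparison, that probability p becomes 1 − p. Neither result can be stated without knowing which arm had PiP.

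**Statistical analysis.** The MVPA regression uses the school mean at follow-up, the school's baseline mean, the number followed up as weight, and an arm code. None of these is specific to PiP, and swapping the labels only reverses the sign of the coefficient, so it can be run on coded arms. The analysis of environment against PiP uptake and attendance cannot, because only five schools have the outcome. The article does not say which comes first, or whether different people do them.

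**Assessors.** The tasks described are anthropometry, questionnaires and recording of injuries and service use. The injury item is worded to fit either arm. Interviews on the acceptability of PiP and observation of sessions would reveal the arm, but the article does not say that the blinded assistants do either. The route to unblinding is what an unblinded parent may say. Since allocation is by school, one remark reveals the arm of a site with about 15 children.

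**The case against.** The strongest reply is that the sentence was meant for the main outcome comparison, that this can be run on coded arms, and that the order of data release belongs in the full protocol or the analysis plan. For the MVPA regression this stands: nothing in the article prevents a blind analysis. It does not rescue the sentence as written, which names the health economists and refers to the data analyses without restriction. A release order in another document could protect the MVPA comparison, but could not make the costing of PiP blind.

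A second reply is that little depends on it. The economic evaluation is exploratory and conditional on reliable data, MVPA is measured by a device, and the results are to be treated as preliminary. This also stands, and it limits the weight of the point. Wear-time processing is partly protected too: non-wear follows a numerical rule, and minimum wear time is derived from baseline data, which are collected before allocation. Matching parents' logs to the device record is the step best finished before arm-revealing data arrive.

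A reader might go further and infer that the assessors' own tasks reveal the arm, so that their blinding also fails. The document does not support this. Disclosure by parents is a risk shared by trials with unblinded participants, its frequency is not given, and visit order and form handling are commonly left to the full protocol. Nor does the risk justify giving injury collection to the trial coordinator, who is unblinded: that would unblind the ascertainment of the injury outcome itself.

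**Conclusion.** The blinding statement is wrong as written. For the health economists the contradiction is certain, given that delivery cost arises only in the PiP arm and belongs in the total per participant. For the statistician it holds for uptake, attendance and withdrawal from PiP, assuming the statistician who compares outcomes also does these analyses. The article places them under the same heading but does not name the analyst. It does not hold for the MVPA comparison, which can be blind if it is completed first.

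Assessor blinding is at risk but not contradicted.

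The size is that of a misdescribed safeguard. Once data from the PiP arm are merged, the analyst knows the arm of all 10 schools. The document gives no basis for putting a figure on bias in any outcome, and none is claimed. The correction is worth making because it is cheap and because this pilot is meant to show what a full trial can achieve.

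**What to change.** (a) In *Randomisation and blinding*, limit analyst blinding to the comparisons of MVPA, anthropometry and questionnaires on coded arms and schools. Say plainly that the economic analysis and the analyses of PiP uptake and attendance are not blinded.

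(b) Complete wear-time decisions and lock those coded comparisons before attendance, fidelity and cost data are released to the analysts. Data on withdrawal from PiP reveal the arm in the same way and should follow the same order.

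(c) Have the assistants record at each follow-up visit whether allocation was revealed, and report the result by arm as a feasibility finding for the full trial.

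The cost is a less favourable blinding statement, a data-release order and one extra tick-box. Sample, intervention and outcomes are unchanged. The tick-box can apply only to visits still to come: *Trial status* reports recruitment for Waves 1 and 2 complete and Wave 3 under way, so the record of assessor unblinding will be partial and should be reported as such.
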